### Data monitoring: Formal committee and interim evaluation

Due to the low-risk nature of the intervention, an independent data monitoring committee will not be established. Instead, oversight responsibilities will be assumed by the principal investigator and designated study staff. Continuous data monitoring will be performed to ensure participant safety and adherence to the study protocol. In the case of unexpected adverse effects or ethical concerns, consultation with an independent expert will be initiated. No formal interim analyses are planned; however, exploratory analyses of trends in biological markers, such as C-reactive protein and CGRP levels, may be conducted to provide descriptive insights into potential physiological changes during the intervention. These analyses will not impact trial progression or design.

### Participant consent

Prior to enrolment, all individuals will be asked to sign a written consent form. This process will be conducted by trained study personnel and will ensure participants fully understand the research objectives, procedures, potential risks and benefits, and their rights, including the ability to withdraw at any stage without penalty. Adequate time and opportunity will be provided for participants to ask questions and receive answers before they decide to participate.

### Consent for future research use

Participants will also have the opportunity to provide additional consent for their anonymized data and biological samples to be retained for use in future, ethically approved research. This consent is entirely optional and will be clearly distinguished from the primary trial agreement. Any secondary use of data or samples will comply with ethical and legal standards and undergo independent review.

### Data confidentiality

All personal information collected during the study will be handled with strict confidentiality. Only data essential to the study’s objectives will be gathered. Identifiable information will be stored securely and separately from research data, with each participant assigned a coded identifier to protect anonymity. After the study concludes, any identifying details will be destroyed or irreversibly anonymized. The remaining data will be stored in secure, access-controlled systems for the legally required duration, after which it will be responsibly disposed of.

### Data sharing and access

As of now, no data have been generated. Upon completion of the trial, anonymized datasets, the study protocol, and the statistical analysis plan will be made available through public repositories aligned with open science practices. Requests for further access to data or supporting materials will be reviewed by the study leadership, subject to ethical constraints and participants’ consent.

### Research ethics approval

The study has received formal approval from the ethics review committees of the two collaborating institutions. Any proposed changes to the protocol will undergo additional ethical review and will be communicated to investigators, study registries, and relevant publication outlets. All research activities will be conducted in accordance with national legal frameworks and internationally recognized ethical principles, including those outlined in the Declaration of Helsinki.

### Adverse events and safety reporting

Participants will be actively monitored for any health-related issues throughout the course of the trial. All health events will be thoroughly documented, evaluated for intensity, and examined to determine any potential connection to the intervention. In the case of serious health events, these will be promptly reported to the appropriate ethics review boards and regulatory institutions in line with applicable policies. A complete account of both non-serious and serious health-related events will be included in final publications and official trial documentation.

In this regard, we will check some screening criteria prior to immersive virtual reality exposure: participants will be screened for conditions that may predispose them to adverse reactions during VR use, including history of epilepsy or photosensitive seizures, severe cibersickness when using the virtual reality hardware, or vestibular disorders. Also, anxiety disorders, claustrophobia, uncorrected visual impairments or balance instability will be considered.

Regarding thresholds for discontinuation, participants will be dropped out from the study if they experience cybersickness (measured by the Fast Motion Sickness Scale), dizziness, musculoskeletal injury, or a persistent increase in pain above 7/10 for more than 2 consecutive sessions, the subject will be excluded from the study. Algo, acute symptoms including moderate to severe nausea, dizziness, disorientation, headache or eye strain persisting beyond 15 minutes post-session, and emotional distress or panic symptoms during exposure are considered for stopping the intervention.

Similarly, and with respect to monitoring procedures, each participant will be supervised by a trained physiotherapist. Also, participants will complete a brief adverse event checklist with the previously mentioned items before and after each session. All adverse events will be documented and reported according to CONSORT guidelines for non-pharmacological interventions.

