#### Experimental group.

Participants in the experimental group will follow a treatment program that combines the standard treatment with an IVR intervention program. For the first 4 weeks, participants will undergo IVR treatment, and in the following 8 weeks, they will follow the same treatment as the control group.

Participants will complete up to 12 sessions of IVR, using a head-mounted display (HMD) of Meta Quest III and a hand tracking system (Meta VR, Facebook, California) to interact with the therapeutic software “Dynamics PainRehab” (Dynamics VR Rehab, Seville, Spain). The Meta Quest III HMD was selected due to its commercial availability, widespread use, minimal visual latency, and ease of use for participants. The “Shoulder PainRehab” app will be used, which features multisensory inputs (visual and auditory), high-quality graphics, and head and hand tracking, allowing for an immersive experience. Additionally, the IVR program will incorporate embodiment strategies via full-body virtual avatars, which have been associated with greater hypoalgesic and sensorimotor effects during IVR interventions (Fig 2).

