**Fig 2 pone.0341215.g002:**
[figure not shown]
Immersive virtual reality multisensory environment with integrated full-body virtual avatar. Dynamics PainRehab® (Dynamics VR Rehab, Seville, Spain). All images have been reproduced with the permission of the respective company, and all rights to these images are owned by the respective rights holders.

Participants will receive an IVR session three times a week for 20 minutes within the virtual environment, completing the necessary 12 training sessions. They will be supervised by an experienced physiotherapist. Prior to the start of the IVR program, all participants will play a familiarization game with the IVR system during 2 sessions, regardless of their clinical assessment findings, to become accustomed to using the VR system.

The behavioral IVR program consists of three weekly sessions, progressing through six levels of difficulty. The program begins with 50% of the shoulder’s range of motion (ROM), with difficulty increasing by 10% increments in maximum ROM, reaching 100% by the final stages. The interventions will be delivered individually to each participant. If the participant experiences adverse effects such as severe cybersickness, dizziness, musculoskeletal injury, or persistent increase in pain exceeding 7/10 for more than two consecutive sessions the intervention will be discontinued.

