## Results

According to the recommendations of the Initiative on Methods, Measurement, and Pain Assessment in Clinical Trials (IMMPACT), this study will incorporate multiple measures to evaluate changes in pain intensity, health-related quality of life and functioning, as well as global ratings of improvement [41]. Similarly, the assessment of domains will follow expert consensus from the OMERACT Shoulder Working Group, aligned with the Core Domain Set for Shoulder Disorders [42].

Clinical and clinimetric outcomes will be assessed at baseline and at follow-ups at 1-, 2- and 3-months following treatment initiation. Biomarkers will be measured at baseline and at 1- and 3-months follow-ups (Figs 1 and 3).

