### Statistics

Data analysis will be performed using SPSS version 30.0 (SPSS Inc., Chicago, IL, USA). Descriptive statistics will be used to summarize the demographic characteristics and baseline clinical, clinimetric and biomarker measurements of the sample. Continuous variables will be reported as mean ± standard deviation (SD), while categorical variables will be presented as frequencies (n) and percentages (%). For quantitative variables that do not follow a normal distribution, the median and interquartile range (IQR) will be used to describe the data.

For the primary analysis, a linear mixed-effects model will be used to compare changes in the dependent variables across the three time points between the two groups. The model will include fixed effects for site (Spain vs Chile) and baseline pain scores, along with group, time, and their interaction, as well as random intercepts for participants to account for within-subject correlations.

In addition to the primary analysis, bivariate correlation analyses (Pearson or Spearman, depending on the distribution of the variables) will be performed to examine the associations between the key variables at each time point.

To explore potential confounding variables, a series of covariate analyses will be performed, adjusting for baseline values of the dependent variables, age, gender, and other relevant demographic or clinical characteristics.

Statistical significance will be set at a p-value of <0.05 for all tests. Effect sizes (Cohen’s d) will be calculated for the main effects of the intervention to assess the magnitude of the group differences, and results will be presented with 95% confidence intervals.

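### One section stops the intervention and another removes the participant from the study for nearly the same adverse events; if the second is followed, obtainable follow-up pain scores are lost

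*Protocol article*

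**What the plan says.** Two sections set stopping rules.

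- **Interventions, Experimental group (text below Fig 2):** "If the participant experiences adverse effects such as severe cybersickness, dizziness, musculoskeletal injury", or a "persistent increase in pain exceeding 7/10 for more than two consecutive sessions the intervention will be discontinued".
- **Adverse events and safety reporting:** "participants will be dropped out from the study if they experience cybersickness (measured by the Fast Motion Sickness Scale), dizziness, musculoskeletal injury", or persistent pain over the same 7/10 threshold. The sentence then repeats its consequence: "the subject will be excluded from the study". The next sentence lists other acute reactions, ending with "emotional distress or panic symptoms during exposure are considered for stopping the intervention".

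Three other sections determine what is at stake.

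- **Timing of IVR** (Experimental group): "For the first 4 weeks, participants will undergo IVR treatment, and in the following 8 weeks" they follow the control programme.
- **Timing of assessments** (Results): "Clinical and clinimetric outcomes will be assessed at baseline and at follow-ups at 1-, 2- and 3-months following treatment initiation". The primary outcome is change from baseline in NPRS.
- **Analysis** (Statistics; Statistical population and handling of missing data): a linear mixed model under intention to treat, valid if data are missing at random. Pattern-mixture or selection models follow only if something suggests otherwise. On the model terms: "The model will include fixed effects for site (Spain vs Chile) and baseline pain scores", plus group, time and their interaction.

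**The concern.** Stopping treatment and leaving the study are different things for an intention-to-treat analysis. Someone who stops the IVR sessions can still rate their pain at each visit, and those ratings are what the analysis needs. Someone removed from the study normally provides none. The protocol prescribes both for nearly the same events, so staff in Spain and Chile cannot tell which to apply.

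The events are not neutral with respect to the comparison. Cybersickness can occur only where IVR is given, and the pain trigger uses a 0-10 pain rating closely related to the primary outcome. Scores lost under the removal rule would therefore be missing for reasons linked to arm or to pain, and the protocol itself would have created the gap.

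**Working it through.** The plan gives no figure for this point, so the check compares the texts and then counts assessments.

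**Step 1. The two rules side by side.**

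| | Experimental group | Adverse events and safety reporting |
|---|---|---|
| Cybersickness | must be severe | measured by a named scale; no severity or cut-off |
| Dizziness | yes | yes |
| Musculoskeletal injury | yes | yes |
| Pain over 7/10 | more than two sessions in a row | more than two sessions in a row |
| Consequence | intervention stops | participant leaves the study (said twice) |

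The triggers match except for cybersickness severity. The consequences do not match.

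**Step 2. Does the text itself separate the two consequences?** Yes. Directly after the removal rule, the adverse-events section uses stopping the intervention as the consequence for other acute symptoms. Dizziness appears in both of its sentences: without qualification it leads to removal, while among symptoms lasting more than 15 minutes after a session it leads only to stopping the intervention.

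**Step 3. Does any section say that assessments continue after removal?** No. Data retention lists general contact and scheduling measures. Care and follow-up for study-related harm concerns clinical care.

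**Step 4. Scores lost per removal.** Planned follow-up scores are at months 1, 2 and 3, taken here as weeks 4, 8 and 12.

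- Removal in weeks 1-4, before the 1-month visit: 3 of 3 lost; only the baseline score remains.
- Removal in weeks 5-8: 2 of 3 lost.
- Removal in weeks 9-12: 1 of 3 lost.

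IVR is confined to weeks 1-4, so a removal for cybersickness normally falls in the first row.

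**Step 5. Scale of one early removal.** With 50 participants at 1:1, the expected arm size is 50 / 2 = 25, giving 25 x 3 = 75 planned follow-up scores per arm. One early removal loses 3 / 75 = 4% of them. The expected number of such removals is not stated.

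**Step 6. Can the analysis make up the loss?** Intention to treat keeps every score recorded before removal, but it cannot supply scores never taken. Statistics enters baseline pain as a fixed effect and refers to three time points without naming them. If these are months 1, 2 and 3, an early removal contributes no outcome record to the model. If baseline is one of the three, it contributes that score only. Either way, the missing follow-up is handled by assumption.

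**The case against.** The strongest reply is that this is loose wording. The removal sentence is grammatically broken and is introduced as a threshold for discontinuation. The section describing the intervention gives the compatible rule, and the analysis section keeps all randomised participants whatever their adherence. On that reading nobody's follow-up ends and nothing is lost. This is plausible, and it limits the point: the loss is conditional on the removal rule being applied. It does not dispose of the point, because removal is stated twice and the next sentence treats stopping the intervention as something different.

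There are also mitigating provisions. Severe dizziness and uncontrolled vestibular disorders are excluded at entry, two familiarisation sessions precede the IVR programme, the sample size allows 10-15% dropout, and models for data not missing at random are foreseen. These may reduce the number of removals or their effect. They do not recover scores that were never collected, and those models are conditional and rest on assumptions that the data cannot test.

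A reader might infer more: that the trial will be biased, perhaps in favour of IVR, or will lose a definite amount of power. The document supports neither. It gives no event rates and no information on how removed participants would differ from those retained. The pain trigger need not be confined to one arm, and removals might fall within the dropout allowance. Any power or bias figure would rest on invented inputs, so none is given. Nor does the text show that ending follow-up was a deliberate choice.

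**Conclusion.** The contradiction is on the page, concerns a rule of trial conduct, and does not depend on anything an analysis plan would supply. It should be fixed. If the adverse-events section is followed as written, each removal loses one to three follow-up pain scores, and all three when it occurs before the 1-month visit. The resulting gaps would be related to arm or to pain, and the primary analysis would have to assume them missing at random although the data could simply be collected.

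The conclusion assumes that removal from the study ends outcome assessment, which is the ordinary meaning and is nowhere contradicted. The 4% per early removal assumes 25 in the arm; simple randomisation may give a somewhat different number. How many participants would be affected, and the direction and size of any bias, remain unknown.

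**What to change.** In Adverse events and safety reporting, replace removal from the study with stopping the IVR or exercise sessions. Require severe cybersickness there, as in the Experimental group section, so that one trigger applies throughout. Add that participants who stop for these reasons continue the 1-, 2- and 3-month assessments and are analysed as randomised unless they withdraw consent.

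The cost is a wording amendment, by the ethical review route the protocol already describes, and a few extra assessments of people who have stopped treatment. Participant protection is unchanged, because the sessions still stop.

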### Care and follow-up for study-related harm

Should any participant experience adverse effects linked to the study, appropriate clinical management—including medical evaluation, treatment, and follow-up—will be provided. Information about available support systems and procedures for managing risks will be communicated during the consent process.

### Dissemination policy: Communication of results

The findings from this research will be communicated through publication in academic journals and presentation at scientific forums. Participants will receive lay summaries explaining the results in accessible language. All study outcomes, whether statistically significant or not, will be disclosed to ensure scientific transparency.

### Dissemination policy: Publication authorship

Eligibility for authorship will be determined in accordance with internationally recognized criteria. Individuals who meet these criteria through substantial contributions to the study’s conception, design, execution, analysis, or interpretation will be listed as authors. The specific roles and contributions of all authors will be transparently disclosed in resulting publications. Other contributors will only be acknowledged as authors if their involvement satisfies these authorship standards; otherwise, they will be appropriately recognized in the acknowledgments section.

### Dissemination policy: Open research and reproducibility

To advance open and reproducible science, all essential research outputs—including the final protocol, anonymized datasets, and statistical scripts—will be made publicly available following primary analysis, in the Open Science Framework repository. Additional documentation, including methodology guides and technical appendices, will be provided to support replication efforts by other researchers.

## Discussion

The IVR-RCRSP-Rehab study aims to examine the clinical impact of novel IVR program in people suffering with RCRSP, who often demonstrate significant interference on daily functioning and quality of life. The current multicentre RCT seeks to assess significant outcomes of an IVR exercise-based intervention that encompasses both clinical and clinimetric variables, as well as pain-related biomarkers such as CRP and CGRP. Besides its impact on clinical outcomes, this study may be useful for the possible implementation of digital technology such as IVR on daily clinical practice of public and private healthcare systems, improving adherence, accessibility and cost-effectiveness in shoulder rehabilitation.

RCRSP is now considered a complex biopsychosocial phenomenon in which different factors interact with each other, influencing both the onset of symptoms and the prognostic course of the patient’s condition [63]. This is reflected in the study by Powell et al. (2022), with 91% of physiotherapists believing that psychosocial constructs are important mechanisms underpinning the potential efficacy of exercise for RCRSP [8]. Within this biopsychosocial perspective on rotator cuff -related pain, a recent study by Delen et al. (2025) showed that higher physical activity levels and health status were associated with a better recovery in patients with RCRSP [64]. However, therapeutic exercise modalities for RCRSP have traditionally been tissue-targeted, and furthermore, the low reproducibility of programmes reported in studies poses a significant challenge to clinical cost-effectiveness [65,13]. The paradigm shift from a tissue-based approach to a personalised multimodal intervention for RCRSP has been encouraged [66], due to high rate of recurrent symptoms, variability in pain trajectories, and uncertainty surrounding the RCRSP management [67,68]. Despite the limited evidence about efficacy of IVR in the treatment of RCRSP, the importance of task-oriented exercise for rotator cuff disorders has been underscored in recent research [69]. IVR may be used to offer a personalised motor learning experience to patients with chronic pain, including task-oriented exercise that may enhance meaningful and challenging daily living activities [70].

First-line treatment recommended by current guidelines for RCRSP includes education, symptom modification strategies and clinician-led exercise within a multimodal physiotherapy programme [71]. Multimodal physiotherapy intervention aims not only to reduce pain, but also to improve neuroplasticity and physical functioning, pain-related psychological factors and ultimately reduce disability and interference from chronic pain [72]. To this end, IVR provides an enriched environment to incorporate a function-focused approach within a multimodal physiotherapy programme, harnessing motivation through IVR-based exercises may enhance outcomes and increase engagement, enjoyment and overall satisfaction. Given that RCRSP is a multidimensional condition, it is critical when considering exercise-based intervention, in which the patient’s engagement and positive expectations within the treatment are extremely important variables. In this context, our study aimed to improve the adherence and satisfaction of RCRSP patients using a tool that, although increasingly used, is still novel for the general population, and the management of shoulder-related disorders.

This study has several strengths that highlight the potential impact of these findings on the management of patients with RCRSP. One of the main assets of this research is its technological innovation, which employs IVR to create safe and gamified experience for rehabilitation. Such motivating experience have shown potential to adapt exercises to the individual needs of patients, thereby improving the treatment efficacy. Our approach does not only facilitate rehabilitation, but also addresses biopsychosocial dimensions of chronic pain, targeting key factors such fear of movement, avoidance behaviour, pain self-efficacy, pain-related biomarkers, strength, disability and quality of life. Moreover, our study includes multiple outcomes based on a conceptual framework, thus providing a multidimensional assessment of the competing IVR interventions. Recently, these potential multidimensional effects have been reported in a study by Ceko et al. (2022), who found that an IVR program in patients with chronic low back pain revealed brain neuroplasticity changes, reduced pain intensity and pain interference, as well as improvements in disability, fear of movement, and pain-related worries [73].

Whereas most IVR research has been focused on acute pain or short time interventions, this study is focused on a prevalent form of chronic pain with a longer time horizon to test for evidence of additional benefits within a first line treatment recommendation. Given the current paucity of rigorous randomized controlled trials evaluating the efficacy of IVR compared to standard care or a wait-and-see approach, there is a pressing need for high-quality evidence to inform clinical decision-making. Encouraging such studies is essential to guide stakeholders in the effective implementation of IVR-based interventions in daily clinical practice. Likewise, establishing adequate dosimetry and reporting user experience factors has been recommended to guide IRV-based exercises in evidence-based clinical practice. The present study follows international recommendations for reporting RCTs, including those of CONSORT and TIDieR, which guarantees the reproducibility of the study, and the interventions performed.

Although the study design and methods have been meticulously considered, several limitations and practical considerations need to be addressed. One potential limitation of the study is the possibility of adverse events such as “cybersickness”, particularly in older adults or those unfamiliar with digital technology. To address this, we have designed a training session with gradual introduction to familiarize participants with the IVR system and will provide ongoing technical support throughout the study. Moreover, participants will be actively monitored for any health-related issues or adverse event throughout the course of the trial.

Although randomization is expected to balance baseline characteristics across groups, residual confounding may still occur, particularly in moderate sample sizes like the one in the present study. Several baseline variables—such as age, sex, duration of symptoms, number of comorbidities, baseline pain intensity, and psychosocial factors are measured and will be included in the analysis to account for their potential influence on outcomes. While these variables are not confounders in the strict sense due to their measurement and planned inclusion in the statistical models, they may still introduce bias if imbalances arise post-randomization. Therefore, we will assess baseline comparability and, if necessary, adjust for relevant covariates using multivariable linear mixed-effects models. All covariates considered for adjustment will be prespecified in the statistical analysis plan.

In this context, another anticipated limitation of the study is the exclusive collection of biomarker data within the Spanish arm. Although this decision was based on logistical and budgetary constraints, it will inherently restrict the generalizability of biomarker-related findings to the broader international sample. To address this, all analyses involving biomarkers will be conducted in a stratified manner and interpreted solely within the context of the Spanish population, and no extrapolation of biomarker findings to the Chilean cohort will be performed. Nevertheless, the shared clinical and psychosocial framework across both cohorts will allow for the exploration of broader associations that may inform future research. Findings related to biomarkers will be considered preliminary and context-specific, serving as a foundation for subsequent studies aiming to validate and expand upon these results in other settings, including the Chilean population.

Additionally, other aspects such as medication use and co-interventions will be monitored and restricted during the study period to minimize external influences. To address this issue, participants will be strongly advised to maintain their regular medication regimen (if applicable) but will not be permitted to initiate any new kind of treatments during the program and follow-up period. Also, sensitivity analyses will be conducted to evaluate the robustness of the findings under different modelling assumptions. The study team shall thoroughly select and monitor participants to ensure compliance with this requirement. Participant dropout during the follow-up period has the potential to limit the study and might affect the validity and generalisability of the results. To mitigate this, we have outlined several adherence strategies, including personalised follow-up, scheduling flexibility, and incentives to maintain participant engagement throughout the trial.

